### Interim analyses {21b}

No interim analysis will be performed.

### Methods for additional analyses (e.g. subgroup analyses) {20b}

No additional or subgroup analyses will be performed as part of the trial

### Methods in analysis to handle protocol nonadherence and any statistical methods to handle missing data {20c}

The analysis to handle protocol nonadherence will follow intention to treat principles. Linear mixed models permit inclusion of all cases even if data could be missing from some timepoints. Missing data will be ignored, rather than imputed.

### Plans to give the full protocol, participant-level data and statistical code {31c}

The full protocol is registered with the ANZCTR and publicly available via their platform. The data sets used and analyzed for this study will be available from the corresponding author on reasonable request.

## Oversight and monitoring

### Composition of the coordinating center and trial steering committee {5d}

The Centre for Neurorehabilitation, Ageing and Balance Research within the School of Health and Rehabilitation Sciences at the University of Queensland is the coordinating center. [name] is the center director who will be responsible for design and conduct of the trial, organizing committee meetings, managing reporting requirements and publication of study results. All investigators and the trial manager are members of the trial management committee who are responsible for reviewing study progress, data and administration management and reviewing trial conduct. This team has all completed the Good Clinical Practice certification in Australia. They meet fortnightly with trial progress reviewed and reported to the funding body and ethics annually.

### Composition of the data monitoring committee, its role and reporting structure {21a}

For this protocol, a DMC is not needed as this is a low-risk intervention (exercise at this level is recommended for all people with PD) and it is not required by the ethics committee and regulatory authorities.

### Adverse event reporting and harms {22}

The risk of harm during assessment, or intervention is small, mitigated by the presence of a physiotherapist experienced in working with people in this population, in a clinical exercise environment and experienced in exercise prescription. Any adverse events that occur during or between intervention sessions will be recorded by the physiotherapist supervising the intervention. At each scheduled assessment time point participants will be asked if any adverse events (related or unrelated to the study) have occurred since the previous assessment. All participants will be asked to contact the researcher responsible for intervention, if they experience any falls, injury or illness that impacts on their movement or exercise during the follow-up period. Minor adverse events and their outcomes are recorded as part of routine data collection. Major adverse events will be reported to the principal investigator and on to the relevant ethics committee as per the reporting requirements of the ethics committee. All harms that occur during the participant’s enrolment in the study will be graded using the Common Terminology Criteria for Adverse Events (CTCAE) Version 5.0 (November 27, 2017) and reported in the results manuscript.

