**Methods:**

This will be an assessor-blinded, randomized controlled trial performed in Brisbane, Australia. Ninety-two people with mild-moderate PD will be randomly allocated to two groups: usual care, and a physiotherapy-led group exercise program combined with self-management strategies. In the intervention group, twelve, 80-min sessions will be conducted over 4 weeks in groups of up to 4 participants. The intervention will consist of circuit training including treadmill walking to target aerobic fitness, and activities targeting strength, balance, and gait performance. In addition, each session will also incorporate strategies focusing on self-management and behaviour change, augmented by the provision of a fitness activity tracker. Outcome measures will be collected at baseline (T1), immediately post intervention (T2) and at 6 months follow-up (T3). The primary outcome measure is free-living physical activity (average daily step count over 7 days) at pre (T1) and post (T2) intervention measured using an activPAL™ device. Secondary outcome measures captured at all time points include time spent walking, sedentary and in moderate intensity exercise over 7 days; spatiotemporal gait performance (step length, gait speed, endurance); health-related quality of life; and outcome expectations and self-efficacy for exercise.

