The self-management approach will be delivered during the same 4-week period that participants are participating in the exercise groups. It will involve 5–10-min sessions, delivered individually to the participants by the physiotherapists prior to or during the exercise sessions. Behaviour change techniques used in this self-management approach will include education, behavioural instruction, self-monitoring, goal setting and goal review, feedback, problem solving, action planning and coping planning to encourage initiation and maintenance of physical activity. At the first exercise session, participants in the intervention group will receive information and a workbook to encourage self-monitoring of physical activity and guide participants through the process of setting short- and long-term goals as well as formulating action plans and coping strategies. During the 4 weeks of exercise sessions and the following 6 months, participants will also be provided with a Garmin Vivosmart fitness tracker that monitors and sets goals for physical activity (number of steps / day), and records heart rate, and distance travelled. Participants will be instructed in how to use the device and associated application/software, and their self-monitoring ability will be tracked during the 4 weeks with the physiotherapist. During the follow-up period participant activity will be monitored monthly via the online Garmin platform. If a reduction in activity level is noted the participant will be contacted by phone to check in and to discuss their physical activity goals and achievements.

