## Participant characteristics

Participant characteristics collected at baseline will include demographic data (age, sex, years since diagnosis), medical history and general health status. To characterize their Parkinson’s disease, at every time point severity of PD will be rated using the Hoehn & Yahr Stage [35]; levodopa equivalent dose will be calculated from their prescribed medication; and the Movement Disorders Society MDS-Unified Parkinson’s disease rating scale motor subsection III [36] and the Freezing of Gait questionnaire [37] will be completed. Exercise self-efficacy will be measured at post and follow-up assessments using the Outcome Expectations for Exercise (OEE) Scale [38] and the Self-efficacy for Exercise Scale (SEEs) [39].

The occurrence and details of any adverse events (e.g. falls), experienced since the last assessment session, will be recorded at the post intervention and follow-up assessments.

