### Plans to promote participant retention and complete follow-up {18b}

All data will be managed with an intention to treat philosophy, including any who deviate from the allocated intervention. Once participants are enrolled in the study, the research team will make every reasonable effort to follow them for the entire study period, including reminding them of upcoming data collection appointments. Participant retention through to follow-up will be optimized by regular contact throughout the intervention and follow-up period for those in the intervention group. Participants in the control group will be contacted between time points to schedule appointments and provide reminders. Any deviations from the study protocol and the trial’s time plan (including withdrawal) or from the intervention will be documented.

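### Adverse events are ascertained more intensively in the intervention arm, mainly from T1 to T2, so a between-arm reading of all reported harms is likely to overstate the programme's harms.

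*Protocol article*

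**What the plan says.** The protocol article describes three ways of capturing adverse events.

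- **Session recording.** Adverse event reporting and harms {22}: "Any adverse events that occur during or between intervention sessions will be recorded by the physiotherapist supervising the intervention". The abstract gives the exposure to this route: "twelve, 80-min sessions will be conducted over 4 weeks in groups of up to 4 participants". Controls have no sessions.
- **Question at assessments, both arms.** The same section: "At each scheduled assessment time point participants will be asked if any adverse events (related or unrelated to the study) have occurred" since the preceding assessment. Participant characteristics places the recording at T2 and T3: events "experienced since the last assessment session, will be recorded at the post intervention and follow-up assessments".
- **Self-report, both arms.** The same harms section: "All participants will be asked to contact the researcher responsible for intervention, if they experience any falls, injury or illness" that affects movement or exercise. This request is tied to the follow-up period.

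Two sections describe further follow-up contact in the intervention arm. Intervention description {11a} has monthly review of tracker data: "If a reduction in activity level is noted the participant will be contacted by phone to check in". The retention section {18b} relies on "regular contact throughout the intervention and follow-up period for those in the intervention group", whereas controls are contacted to book appointments and give reminders.

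The harms section closes by stating that all harms will be graded with CTCAE version 5.0 and reported in the results paper. It does not separate them by route of capture, and it states no between-arm comparison or test of harms.

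**The concern.** The chance that an event is recorded depends on the arm. A minor strain or a fall without injury in week 2 can be mentioned to a physiotherapist within days in the intervention arm. In a control it has to be remembered at T2. If the true rates are equal, more events will tend to be recorded in the intervention arm. If the true rates differ, the recorded excess mixes real harm with better detection.

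Even with no formal test planned, readers of a two-arm trial will compare the harms reported for each arm. Falls and minor events are the most exposed. They matter for an exercise programme in Parkinson's disease, and the protocol itself gives falls as its example of an adverse event. The harms account could make the programme look less safe than it is, or leave a true excess uninterpretable. The estimate of steps per day does not depend on any of this.

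**Working it through.** **Step 1. Stated capture routes by period and arm**

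| Period | Intervention | Control |
|---|---|---|
| T1 to T2 | Recording at 12 sessions, plus the question at T2 | Question at T2 |
| T2 to T3 | Question at T3, self-report request, monthly tracker review with a call if activity falls, regular contact | Question at T3, self-report request, contact for scheduling and reminders |

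The imbalance is clear from T1 to T2. It is smaller afterwards, because the two main routes are shared and neither section on the additional contact says that adverse events are asked about. The contact could still bring events to light: a fall or illness can lower activity and so prompt a call.

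**Step 2. Size within the programme window**

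The plan gives no adverse event rate and no capture rate, so it has no figure to reproduce. Everything below is assumption.

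Let the true risk be equal in both arms, with capture c_I in the intervention arm and c_C in controls. The apparent ratio is c_I / c_C. Assume c_I of 0.90 to 0.95 and c_C of 0.60 to 0.80.

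- Low end: 0.90 / 0.80 = 1.125, about 1.1.
- High end: 0.95 / 0.60 = 1.583, about 1.6.

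**Step 3. A second model as a check**

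Let recall find a share r of events in both arms, and let session recording independently find a share s in the intervention arm. The ratio is [1 − (1 − r)(1 − s)] / r.

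| r | s = 0.5 | s = 0.9 |
|---|---|---|
| 0.60 | 0.80 / 0.60 = 1.33 | 0.96 / 0.60 = 1.60 |
| 0.80 | 0.90 / 0.80 = 1.125 | 0.98 / 0.80 = 1.225 |
| 0.95 | 0.975 / 0.95 = 1.03 | 0.995 / 0.95 = 1.05 |

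The two models agree for recall of 60-80%. With recall of 95% the effect almost disappears.

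On the absolute scale, take a true risk of 10% to 40% and the same ranges of r and s. The spurious difference then runs from 0.10 × (0.975 − 0.95) = 0.0025, about 0.3 percentage points, to 0.40 × (0.96 − 0.60) = 0.144, about 14 percentage points. With 46 per arm, the chance of a nominally significant difference runs from about 3% to 32%. This is an illustration only, since no such test is planned.

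**Step 4. Size over the whole trial**

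Sessions occupy 4 weeks, and Participant timeline {13} puts T3 at week 26. Assume a constant event rate and equal capture c_C in both arms over the other 22 weeks. The ratio of recorded events is (4 × c_I + 22 × c_C) / (26 × c_C).

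- Low end: (3.6 + 17.6) / 20.8 = 1.02.
- High end: (3.8 + 13.2) / 15.6 = 1.09.

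Extra intervention-arm contact in follow-up could raise these values somewhat.

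**Step 5. After the fix**

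If the comparison uses only answers to the same question, and recall is equal in the two arms, the expected ratio under equal true risk is 1.00.

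**The case against.** The strongest reply is that recording events at supervised sessions is inherent in comparing a supervised programme with usual care and is right for safety. No comparison of harms is planned, and how harms are tabulated may be left to an analysis plan that is not shown. This is largely fair. It means the point concerns the collection scheme that the article does state and how its output may be read. It is not an error in a specified analysis.

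Three stronger readings are tempting, and the document does not support them.

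- *A reader might infer that controls are covered only by recall at two visits.* That holds from T1 to T2. In follow-up, all participants are asked to report falls, injury or illness. This shared route may still work unevenly, because reports go to the researcher responsible for intervention, whose team controls are described as meeting only at the allocation call.
- *A reader might infer that the trial has planned a biased comparison.* The article says that harms will be graded and reported. It specifies no between-arm test or table.
- *A reader might take 1.1 to 1.6 as the distortion for the trial.* That range applies to the programme window under assumed capture rates. Recall at T2 reaches back only about 5 weeks and may be fairly complete.

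A further objection is that asking the same question need not give equal capture. People who have discussed events at 12 sessions may recall more at T2, or may leave out what they have already reported. This stands as a limit on the fix.

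**Conclusion.** The concern holds as a likely imbalance in ascertainment, concentrated between T1 and T2. Because all harms are to be reported without regard to how they came to light, a reading by arm will probably overstate the programme's harms. The direction is likely; the size cannot be settled from the document. The ratios of about 1.1 to 1.6 in the programme window and 1.02 to 1.09 over 26 weeks rest on assumed capture of 90-95% against 60-80%. The second range also needs a constant event rate and equal capture outside the 4 weeks. If recall is almost complete, the ratio is near 1. The primary outcome is not affected. This is a cheap improvement to the harms reporting and does not put the trial's main conclusion in doubt.

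**What to change.** - Add a source field to the adverse event record: session, other contact, self-report, or question at T2 or T3. An event found by more than one route carries each flag.
- State that any between-arm comparison of harms uses events elicited by the same scripted question at T2 and T3 in all participants. Put the question after outcome testing, so that an answer about the sessions cannot unblind the assessor beforehand. The question covers everything since the previous assessment, so in-session events can still enter the comparison.
- List session-logged, contact-logged and self-reported events separately by source and arm, with a note that capture was unequal.
- Leave safety recording and reporting as they are.

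The cost is some wording and one form field. The comparative table may omit session-logged events that are not recalled at T2, although these still appear in the separate listing. Equal recall in the two arms remains an assumption and should be stated beside the table.

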### Frequency and plans for auditing trial conduct {23}

Trial conduct will be audited by reviewing data quality every 6 months. This will include review of recruitment rates, source documents, data collection, data entry and adverse events. Reports including recruitment rate, impacts to the trial (e.g. impact of COVID-19), deviations from the protocol and adverse events will be prepared for annual reports to the submission to the funding body and ethics committee. Any project approved by the University Human Research Ethics Committee may be audited at random.

### Plans for communicating important protocol amendments to relevant parties (e.g. trial participants, ethical committees) {25}

Any protocol amendments will be agreed by the trial management committee and must be submitted and approved by the relevant ethics committees. They will also be reported to the funding agency and the clinical trial registry updated.

### Dissemination plans {31a}

The trial results will be disseminated to health care professionals and the scientific community via both publication of the results in relevant journals and presentation of the results at conferences. Results will be included in the completion report for the ANZCTR and the funding body. A summary of the results will be disseminated directly to all participants on completion of data collection.

## Discussion

This trial evaluates a multi-modal intervention designed to improve the volume of free-living physical activity in people with Parkinson’s disease. It uses a novel approach of combining supervised group exercise intervention with behavioural counselling and the provision of an activity tracker to facilitate self-management.

It is expected that this combination of structured exercise and self-management will be effective in firstly improving average daily step count immediately post training as an indication of free-living physical activity but will also importantly give people with PD the training and skills to maintain these improvements for the following 6 months. The intervention has been designed to enhance participants’ motivation to engage in physical activity in several ways. Participants will gain evidence of their competence to exercise via feedback from their physiotherapist and other participants in their exercise sessions, in addition to feedback from their fitness tracker. The self-management approach builds self-regulatory skills and strategies to enable people with PD to create goals related to physical activity and make informed decisions about their activity outside the training sessions, thus building autonomy. In addition, the ongoing use of accelerometers allows participants to track their own activity levels, rather than relying on research staff. Providing the intervention in group sessions facilitates social engagement and support, and helps people feel part of a group, which can contribute to motivation.

Results of this study are likely to add to the growing body of knowledge on the development of approaches to optimize walking in people with PD. Identifying interventions that can assist people with PD to increase their levels of physical activity has the potential to maintain health, walking ability and quality of life for longer.

## Limitations

The authors acknowledge the following limitations: lack of a cost-effectiveness analysis, and limited patient and public involvement in the design of the intervention.

## Trial status

The trial is ongoing and participant recruitment has not been completed. Protocol version 1.0 was approved on Dec 9, 2016. Recruitment began on August 25, 2017. Significant delays to recruitment have occurred from February 2020 due to COVID-19. Approximate date when recruitment will be completed: September 2023. Significant time pressure on the investigative team during COVID-19 also resulted in delays to the completion of this manuscript.

## Abbreviations

PD: Parkinson’s disease
HR: Heart rate
HRR: Heart rate reserve
MoCA: Montreal Cognitive Assessment
1RM: One Repeat Maximum
QOL: Quality of life
PDQ-39: 39-Item - Parkinson’s disease questionnaire
OEE: Outcome Expectations for Exercise Scale
SEEs: Self-efficacy for Exercise Scale
